## Methods/Design

### Study design

A multicenter, prospective observational cohort study in which patients starting treatment with erlotinib will be followed for a period up to 16 weeks. At baseline and in weeks 3-4, 8-9, 12 and 15-16, patients will be asked to fill out a questionnaire. Furthermore, in weeks 3-4, 8-9 and 15-16, blood samples are collected, which will be analysed for plasma concentration of erlotinib. Adherence will be measured using a medication event monitoring system (MEMS). Information from the physician will be retrieved from the patient treatment file.

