#### Questionnaires

The patients will be asked to fill out five questionnaires spread over 16 weeks. The first questionnaire (t = 0) contains questions on patient characteristics, smoking, co-medication, side-effects, quality of life, and patients beliefs and attitude towards disease and medication. In weeks 3-4, 8-9 and 15-16 patients will be asked to fill out an elaborate questionnaire containing questions determining the adherence behaviour, side-effects, dose adjustment, co-medication, quality of life, and patients beliefs and attitude towards disease and medication. In week 12 patients are asked to fill out a short questionnaire containing only questions determining the adherence behaviour, side effects, and dose adjustment. Discontinuation and reasons for discontinuation will be asked in a short questionnaire when a patient stops the erlotinib treatment prematurely.

The questionnaires contain the following items:

1. MARS (Medication Adherence Report Scale) [40,41]. This questionnaire contains statements about adherence behaviour.

2. Nature and grade of the side-effects in a five-point scale.

3. Quality of life measured with SF-12 Health Survey [42,43]. The SF-12 is a short version of the SF-36 and is a validated method to measure quality of life.

4. Attitude towards disease measured with Brief Illness Perception Questionnaire (Brief IPQ) [21]. The Brief IPQ is a validated method to measure the attitude towards disease.

5. Beliefs and attitude towards medicines measured with Beliefs about Medicines Questionnaire (BMQ) [22]. The BMQ is a validated questionnaire. It is divided in two parts, the BMQ general and the BMQ specific. BMQ general measures the patient's beliefs and attitude towards medicines in general. The BMQ specific is specified for erlotinib.

6. Patient characteristics: date of birth, gender, socio-economic status and smoking (current smoking and never/previous smoking).

7. Dose adjustments by the patient. Dose adjustments introduced by the doctor will be derived from the patient file.

8. Co-medication.

9. Discontinuation and reasons for discontinuation. Discontinuation is also derived from the patient file.

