#### Blood sample and laboratory test

A plasma sample will be collected at visits of the patient at week 3-4, 8-9 and 15-16. This blood sample will be drawn simultaneously with the regular treatment's related blood sampling. At these visits patients are asked when they had their last meal and at what time they took their last erlotinib medication. Patients are supposed to take erlotinib at least one hour before or two hours after a meal [31]. Adherence to the instruction will be taken into account in the analysis of the study results.

Apart from that, the time of the blood sample will be documented. Plasma concentrations of erlotinib will be analyzed by LC-MS/MS. The pharmacokinetic parameters AUC, C_max _and C_through _will be derived using the pharmacokinetic model as described by Lu et al [36]. The concentration ratio (CR) is defined as the measured erlotinib concentration divided by the mean population erlotinib concentration that is predicted by the model. To calculate the AUC, C_max_, C_through _and CR the following covariates are measured and used as input for the model: gender, serum albumin, serum total bilirubin, serum α1-acid glycoprotein, calculated creatinine clearance and smoking status [36]. The calculated AUC, C_max_, C_through _and CR will be compared with the data on adherence from the questionnaires and the electronic monitoring system to study the relationship between adherence and the plasma concentration of erlotinib.

Patients are asked about their co-medication in the questionnaires. The data on co-administration of inhibitors of CYP1A2 and CYP3A4, inductors of CYP3A4 and antacids will be examined as covariables.

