### Statistics

The data will be described by means of frequency analysis. Correlation coefficients will be calculated for relationships between adherence, patient characteristics, disease characteristics, side effects, quality of life, patient beliefs and attitude towards disease and medication, dose adjustments and plasma concentration of erlotinib in patients with NSCLC. In particular, the correlation coefficient between plasma concentration and side-effects; the relationship between dose and plasma concentration in daily practice; the influence of different factors on adherence; the influence of different factors on side-effects; the influence of different factors on quality of life; the influence of different factors on dose adjustment and discontinuation. By the use of a multivariate regression analysis the influence of adherence (dependent variable) on plasma concentration and the influence of side-effects (dependent variable) on adherence will be calculated. The dependent variables will be adjusted for potential confounders. For all analyses a two-tailed significance level will be 0.05, all p values below this level will be considered statistically significant. The statistical analyses will be performed with SPSS 15.0 (SPSS Inc. Chicago, Illinois, USA).

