## Discussion

The present study aims to get more insight into patients' experiences with the use of erlotinib in daily practice. We expect variability in the adherence in the general oncology population. This may be complicated by the inter-patient variability in the pharmacokinetics. We hypothesize that side-effects play an important role in the way patients use erlotinib. Therefore, the relationship between self-reported side-effects and adherence is also defined as a main objective. To get more insight into other factors related to adherence and other aspects of the use at home, the effects of determinants are studied in an explorative manner.

We expect that the present study will provide valuable knowledge on patients' experiences with the use of erlotinib. This knowledge will be useful for health care professionals to develop specific interventions to support patients thus improving the adherence and persistence with the use of erlotinib in order to derive optimal benefit from the medication.

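### The rule that every p value below 0.05 is significant covers the exploratory analyses as well as the two main relationships, so at least one false-positive claim is likely

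*Protocol article*

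**What the plan says.** The protocol article fixes one criterion for the whole study (Statistics): "For all analyses a two-tailed significance level will be 0.05, all p values below this level will be considered statistically significant".

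The same section gives that criterion a wide field:

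- It opens with a general statement, "Correlation coefficients will be calculated for relationships between adherence, patient characteristics, disease characteristics, side effects, quality of life", and the list continues with beliefs and attitudes, dose adjustments and plasma concentration. That makes eight groups of variables.
- It then adds several families of unspecified factors, ending with "the influence of different factors on dose adjustment and discontinuation".
- It assigns the two main relationships to an adjusted regression.

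The section on the blood sample and laboratory test says that four pharmacokinetic measures (AUC, Cmax, trough and the concentration ratio) "will be compared with the data on adherence from the questionnaires and the electronic monitoring system".

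Elsewhere the article ranks its questions. Objectives makes two relationships primary: adherence with plasma concentration, and adherence with side-effects. The remaining relationships are to be explored. The Discussion repeats this and says that "the effects of determinants are studied in an explorative manner".

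**The concern.** The article calls most of its analyses exploratory and then commits to declaring each of them significant whenever p falls below 0.05. The ranking in Objectives and Discussion therefore has no effect on what may be claimed. This is an explicit rule, and following it as written would present some chance correlations as established findings.

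The Discussion expects the knowledge gained to help professionals develop interventions that support patients. In a cohort of 65, a chance correlation with a patient belief or characteristic, reported as significant, could misdirect that work.

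The main relationships raise a smaller version of the same issue. There are two of them, each at the full 0.05, and the article's text allows more than one comparison for the first.

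**Working it through.** **The plan's own figures.** The article states a per-test two-sided level of 0.05 and a sample of 65. It states no number of tests and no overall error rate, so there is no multiplicity figure to reproduce. Nor can 65 be reproduced, because the article as shown gives no effect size or power.

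**Formula.** For k independent tests with no true association, the chance of at least one false positive is 1 − 0.95^k and the expected number is 0.05 × k.

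**Counts taken from the article.**

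| Family | k | At least one | Expected |
|---|---|---|---|
| Two main relationships, one test each | 2 | 1 − 0.95² = 9.75% | 0.10 |
| Four pharmacokinetic measures × two adherence sources | 8 | 33.7% | 0.40 |
| Pairs among eight groups: 8 × 7 / 2 | 28 | 76.2% | 1.40 |
| Named variables, tested pairwise across groups | 171 | 99.98% | 8.55 |

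The last row rests on an assumed count of the variables named: 2 adherence, 4 patient characteristics, 2 disease characteristics, 2 side-effect measures, 1 quality of life, 3 beliefs (Brief IPQ and two BMQ parts), 2 dose adjustment and 4 pharmacokinetic, which is 20. All pairs: 20 × 19 / 2 = 190. Pairs within a group: 1 + 6 + 1 + 1 + 0 + 3 + 1 + 6 = 19. Hence 190 − 19 = 171, at one time point.

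**Where 95% is passed.** ln(0.05) / ln(0.95) = 58.4, so 59 independent null tests are needed.

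**Sensitivity to correlation.** Simulation with n = 65, 4,000 runs and no true association between groups:

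- 171 pairs: the chance of at least one false positive goes from 99.98% at within-group correlation 0.3 to 96.2% at 0.9.
- Pharmacokinetics against adherence alone, with 12 and 6 values over three visits (72 pairs, including cross-visit pairs): from 94% to 27% over the same range.

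Correlation does not change the expected number of false positives.

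**Sensitivity to real associations** (independent tests):

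- 28 pairs, half truly null: 1 − 0.95^14 = 51%, with 0.7 expected. One quarter null: 1 − 0.95^7 = 30%, with 0.35 expected.
- 171 pairs, half null: 98.8%. One quarter null: 88.8%.

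**Cost of dividing the level between two main tests.** By Fisher's z, the detectable r is tanh[(z for the level + 0.842) / √(65 − 3)] at 80% power.

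- Two-sided 0.05: tanh(2.802 / 7.874) = 0.34.
- Two-sided 0.025: tanh(3.083 / 7.874) = 0.37.

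**The case against.** **Formal control is not obligatory here.** An observational and largely exploratory cohort need not adjust for multiplicity, and detail of this kind often sits in a full protocol or analysis plan. This stands, and it limits the remedy. It does not excuse the sentence, which positively promises a significance claim for every analysis. If the analyses are exploratory, that is a reason not to promise it.

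**The probabilities assume independence and no real associations.** Both assumptions are doubtful. AUC, Cmax and trough come from one published model, and the concentration ratio divides the measured value by that model's prediction, so these measures should be strongly correlated. The Background itself cites evidence linking smoking to concentration, exposure to rash, and medication beliefs to adherence. This stands, and the sensitivity figures show how much it matters.

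**Stronger readings.** A reader might infer any of the following, but the article does not support them:

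- *That false positives are almost certain.* At 28 independent null tests the chance is 76%. It passes 95% only from 59 such tests, or on the 171-pair count, which is an assumption about how the named variables will be used.
- *That the main relationships amount to 40 tests.* Multiplying by three blood visits (4 × 2 × 3 = 24) and by four questionnaires for side-effects (2 × 2 × 4 = 16) presumes separate testing at each visit. The article does not say this. Its wording on blood samples supports 4 × 2 = 8 comparisons.
- *That every group of variables has subscales.* Only the BMQ is described as having parts.
- *That main and chance findings cannot be told apart at all.* Objectives and Discussion set out the ranking, and Statistics gives the two main relationships an adjusted regression. Only the significance rule ignores it.

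**Conclusion.** The point holds as a badly fixed rule. One significance criterion is applied to all analyses, in conflict with the article's own separation of two main relationships from exploratory ones.

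At least one false-positive claim is likely, but not certain. The central figure of 76% with 1.4 expected assumes one test per pair of groups, independence and no true associations. The figure above 95% also needs pairwise testing of all named variables. If half of the 28 associations are real, the chance falls to about 51%. The 9.75% for the two main relationships also assumes independence, both being null, and one test each.

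No treatment or licensing decision depends on these p values. The defect affects how far the reported associations can be trusted, and it should be corrected.

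**What to change.** In Statistics, replace the blanket sentence with wording to this effect: statistical significance will be claimed only for one prespecified test of adherence with plasma concentration and one prespecified test of adherence with side-effects, controlled together at a two-sided 0.05 (for example by Holm: the smaller p value against 0.025, then the other against 0.05); all other analyses are exploratory and will be reported as estimates with 95% confidence intervals, without claims of significance.

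The sponsor must then name, for each main relationship, the one measure and analysis that carries the claim. Which pharmacokinetic measure, which adherence source and how visits are combined are the sponsor's choices, and so is the method of control. The remaining pharmacokinetic and adherence comparisons can stay as supporting estimates.

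The cost is mainly wording, plus that choice. The loss is the rise in detectable correlation from about 0.34 to 0.37 for the stricter test. Those two figures assume 65 patients with complete data and an unadjusted correlation. Early discontinuation would leave less information and raise both, and the planned adjustment for confounders could change them as well.

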## Discussion

The present study aims to get more insight into patients' experiences with the use of erlotinib in daily practice. We expect variability in the adherence in the general oncology population. This may be complicated by the inter-patient variability in the pharmacokinetics. We hypothesize that side-effects play an important role in the way patients use erlotinib. Therefore, the relationship between self-reported side-effects and adherence is also defined as a main objective. To get more insight into other factors related to adherence and other aspects of the use at home, the effects of determinants are studied in an explorative manner.

We expect that the present study will provide valuable knowledge on patients' experiences with the use of erlotinib. This knowledge will be useful for health care professionals to develop specific interventions to support patients thus improving the adherence and persistence with the use of erlotinib in order to derive optimal benefit from the medication.
